## 5.3. STUDY POPULATION

Within the seven sub-counties of the study area, there are 22 lower-level government run health facilities, including 17 level II health centers, and 5 level III health centers; 20 will be included in ACT PRIME. These 20 health centers will be randomly allocated to the health facility intervention arm or the standard care arm for a total of 10 health facilities in each arm. Clusters to be included in ACT PRIME are defined as the catchment areas of the health centers including households that are located within a 2 km radius of the facilities. Only households located within the clusters will be included in the sampling frame for ACT PRIME. ACT PROCESS follows the same sampling frame as ACT PRIME; participants for each type of data collection methodology are defined below.

### **5.3.1. Self-filled questionnaires**

Our target is to have one self-filled questionnaire completed by all HFI training participants and trainers for each module. There are 5 trainers and approximately 30 health center staff attending 10 module topics. We will conduct up to 350 self-filled questionnaires.

### **5.3.2. Health worker communication assessments + patient exit interviews**

We aim to conduct communication assessments with at least one health worker in each health facility in both the HFI and standard care arms (10 in each arm). Each communication assessment will consist of at least three, and no more than five, health worker/caregiver interaction records. The communication assessments will be conducted immediately before and up to 6 weeks after the HFI training in patient-centered services, and then approximately six months following the training for a total of three cycles. The same health workers will be assessed at each time point to evaluate for changes over time. We will evaluate approximately 20-25 health workers chosen by convenience sampling. Therefore conducting up to 125 health worker/caregiver interactions in each time period; 375 in total, depending on the number of health workers and patients available at the health centers on the days of the study. One health worker will be chosen from each of the level II health centers, and 1-2 health workers will be chosen from each of the level III centers. Exit interviews will be conducted with all consenting caregivers who participated in the assessments, up to a maximum of 125 interviews at each time point, 375 in total.

### **5.3.3. In-depth interviews**

We will conduct up to 25 IDIs with different target populations including HFI implementers (up to 5 interviews), health workers in the HFI arm (up to 10 interviews), and key local and district stakeholders (up to 10 interviews).

### **5.3.4. Semi-structured questionnaires**

We will conduct up to 30 interviews to complete semi-structured questionnaires with different target populations including health workers in the HFI arm (up to 10 interviews), health workers in the standard care arm (up to 10 interviews), and private drug shop workers (up to 10 interviews). For the health worker interviews, we will target the in-charges of the health facilities.

### **5.3.5. Focus group discussions**

We will conduct up to 16 FGDs with primary caregivers and community health workers from the study area selected by convenience sampling.

## **5.4. SELF-FILLED QUESTIONNAIRES**

Self-filled questionnaires for each training module will be completed by all staff participants and trainers (Table 5.1). The purpose of the self-filled questionnaires is to gather opinions from participants and trainer on the objectives, content, materials, and implementation of the HFI training modules. Self-filled questionnaires will be completed at the end of each training topic. Training

modules, topics and associated self-filled questionnaires found in the Appendices are outlined in Table 5.1.

All health center staff will be invited to participate in the training module relevant to their position as outlined in Table 5.1. At the beginning of the training, written informed consent to complete the self-filled questionnaires will be obtained from all participants (Appendix B) as outlined in section 8.2. Self-filled questionnaires will be completed directly after the training topic and collected by the study team.

**Table 5.1 Health worker training modules, topics and self-filled questionnaires**

| Module                    | Participants   | Topics                                                                                                                                                            | Appendix |              |
|---------------------------|----------------|-------------------------------------------------------------------------------------------------------------------------------------------------------------------|----------|--------------|
|                           |                |                                                                                                                                                                   | Trainers | Participants |
| Health center management  | In-charges     | Budgeting and accounting
Supply management
Information management                                                                                           | C        | D            |
| Fever case management     | Clinical staff | Fever case management                                                                                                                                             | E        | F            |
| Patient-centered services | Clinical staff | Introduction to PCS and self-observation
Improving interactions with patients I & II
Improving interactions with colleagues
Improving the patient visits | G        | H            |
| Patient-centered services | Support staff  | Improving the patient visit                                                                                                                                       | G        | H            |

## **5.5. HEALTH WORKER COMMUNICATION ASSESSMENTS AND PATIENT EXIT INTERVIEWS**

We plan to conduct communication assessments with health workers from both the HFI and standard care arms. The purpose of the assessments is to evaluate and compare the communication between health workers and patients immediately before and after HFI training in ‘communicating with patients’ and then during the study period. Health worker/caregiver interactions during consultations will be audiotaped and assessed using a validated measurement methodology, the Measurement of Patient-Centered Communication (MPCC) (Appendix I). The MPCC scores assessments according to three elements of patient-centered communication: 1) exploring the disease and the illness experience, 2) understanding the whole person, and 3) finding common ground [44]. In addition to the recorded interactions, consenting caregivers will be interviewed immediately on exit from the consultation to give their view of the quality of the interaction with the health worker. The purpose of the interviews is to determine the level of satisfaction of caregiver with the health facility visit.

Health workers from both the HFI and standard care arms available on the day of the communication assessment will be selected using convenience sampling, and invited to participate. At least one health worker from each facility, will be included. At least three interactions, and up to five interactions, will be recorded with each health worker. Written informed consent to conduct the assessments will be obtained from health workers before beginning (Appendix J) as outlined in section 8.2. Demographic information on the health worker will then be obtained (Appendix K).

Once a health worker has been selected and provided informed consent, caregivers who will have a consultation with that health worker will be selected using convenience sampling from the available patients visiting the health center on the day of the health worker communication assessment.

Patients to be included in the communication assessments will be 'typical uncomplicated malaria patients'. Inclusion criteria are 1) age: a child under five years of age, 2) fever or suspected fever, and 3) agreement of caregiver to provide informed consent. Exclusion criterion is 1) danger signs of severe disease (Appendix L). The same caregivers will be invited to participate in an exit interview after the consultation (Appendix O). Written informed consent to conduct the assessments, and the exit interviews, will be obtained from caregivers before beginning (Appendix M) as outlined in section 8.2. Demographic information on the caregiver will then be obtained (Appendix N).

The communication assessments will be conducted immediately before and up to 6 weeks after the HFI training in 'improving interactions with patients' and then approximately six months following the training for a total of three cycles. The same health workers will be evaluated in each cycle of the assessments.

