## APPENDIX M. HEALTH WORKER COMMUNICATION ASSESSMENTS and PATIENT EXIT INTERVIEWS

**APPENDIX N. HEALTH WORKER COMMUNICATION ASSESSMENT****PART 1: CAREGIVER DETAILS**

|                                                                       |                                  |                                                                  |                                                           |
|-----------------------------------------------------------------------|----------------------------------|------------------------------------------------------------------|-----------------------------------------------------------|
| Health center code
[ ][ ]                                   | Patient ID code
[ ][ ] | Interviewer code
[ ][ ]                                | Date
[ ][ ] / [ ][ ] / [ ][ ]
day month year |
| 1. Number of patients brought by the caregiver today
[ ][ ] |                                  | 2. Number of eligible children being seen today
[ ][ ] |                                                           |

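### Caregivers for the recorded consultations and exit interviews are chosen by convenience, with no rule for which eligible patients are approached, so selection can differ by arm or round

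*Supplement*

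**What the plan says.** The communication assessments cover facilities in both arms: section 5.3.2 plans at least one worker "in each health facility in both the HFI and standard care arms (10 in each arm"). On numbers it says "We will evaluate approximately 20-25 health workers chosen by convenience sampling". Section 5.5 adds "At least three interactions, and up to five interactions, will be recorded with each health worker", and there are three rounds: before the patient-centred services training, up to six weeks after it, and about six months after it. The same workers are assessed each time.

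Within a worker's session, section 5.5 states that "caregivers who will have a consultation with that health worker will be selected using convenience sampling from the available patients". It describes the target thus: "Patients to be included in the communication assessments will be 'typical uncomplicated malaria patients". Fixed criteria follow at once: "Inclusion criteria are 1) age: a child under five years of age, 2) fever or suspected fever, and 3) agreement of caregiver" to give consent; "Exclusion criterion is 1) danger signs of severe disease". Appendix L applies these as coded include/exclude boxes.

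The same caregivers are then invited to the exit interview. Section 7.1 compares categorical exit-interview variables by chi-square or Fisher's exact test, with two-sided significance at p<0.05. Section 7.2 analyses the communication (MPCC) scores descriptively and mentions no case-mix adjustment.

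**The concern.** The criteria say who may be enrolled, not which eligible children are taken when more than three to five are waiting. That choice is left to staff in a component whose stated purpose is to compare communication before and after training, in both arms.

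Three features expose the choice. Patients are recruited after the facilities have been randomised. The rounds are defined by their timing around the training, so recruiters know which round they are in. And the protocol describes no masking of recruiters to arm. Section 5.1 does provide a field team separate from the ACT PRIME team, but under section 8.2.1 ACT PROCESS personnel also obtain consent from trainers and trainees at the intervention training, so some of them can know which workers were trained.

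An easier consultation or a more forthcoming caregiver could raise both the recorded score and the satisfaction answers, whatever the worker has learned. Because one set of caregivers supplies both measures, a selection difference would affect both in the same study.

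**Working it through.** **The plan's own figures.** The ceilings reproduce: 25 workers × 5 interactions = 125 per round, and 125 × 3 rounds = 375. The floor is 20 × 3 = 60 per round, or 180 in total.

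**Where the bias enters.** Let δ be the mean score of the patients taken minus the mean score of all eligible patients, for a given arm and round.
- Bias in the arm difference at round t = δ(HFI, t) − δ(standard care, t).
- Bias in the difference in change from round 1 = [δ(HFI, t) − δ(HFI, 1)] − [δ(standard care, t) − δ(standard care, 1)].

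The second expression is zero if selection is stable over rounds within each arm, or drifts equally in both. Patients are chosen afresh each round, and no passage secures either condition. The number of patients per worker does not appear in these expressions: for a given δ, it governs noise, not bias.

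**What a given shift would do.** The documents give no SD, intracluster correlation or effect size for this component. Assumptions: total SD = 1; correlation within worker ρ = 0.05 to 0.5; J = 10 or 12.5 workers per arm (20 or 25 split equally); m = 3 or 5 patients; normal approximation with a test that allows for clustering by worker.

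SE of the arm difference in one round = √{2[ρ + (1−ρ)/m]/J}.
- Largest: ρ = 0.5, m = 3, J = 10: √{2 × 0.667/10} = 0.365.
- Smallest: ρ = 0.05, m = 5, J = 12.5: √{2 × 0.24/12.5} = 0.196.

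With no true effect and a selection shift b between arms, P(p<0.05) = 1 − Φ(1.96 − b/SE) + Φ(−1.96 − b/SE). Over the whole grid:

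| b (SD) | P(p<0.05), no true effect |
|---|---|
| 0.1 | 0.059 to 0.080 |
| 0.2 | 0.085 to 0.175 |
| 0.3 | 0.130 to 0.334 |
| 0.5 | 0.278 to 0.723 |

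For change from baseline, SE = √{2 × [2(1−ρ)/m]/J}, with ρ = 0.2 or 0.5. A differential shift of 0.3 SD then gives 0.151 to 0.389.

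Selection can also hide an effect. With a true difference of 0.8 SD and ρ = 0.2, a shift of 0.3 SD in the opposite direction lowers power from 0.745 to 0.373 (J = 10, m = 3), or from 0.915 to 0.549 (J = 12.5, m = 5).

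These probabilities bear on the exit interviews, which are tested, and only approximately, since many of those items are categorical. For the MPCC scores the consequence is a shift of size b in the reported means.

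**The case against.** The strongest reply is that the design already contains much of what is needed. The same workers are assessed before training in both arms, so selection that works alike across rounds cancels in the change. Appendix L has a screening number and coded exclusions, including refusal of consent. Appendix N records caregiver age, gender, education and earlier attendance, and the child's presenting problems, so case mix can be compared. Section 6.2 promises written procedures for all activities. The stakes are also limited: MPCC scores are only described, no ACT PRIME primary outcome depends on this component, and at a small centre convenience may amount to taking everyone eligible. No queue sizes are given.

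Most of that stands and limits the importance of the point. It does not settle the order of approach. The baseline safeguard is conditional, the plan states no use of the case-mix data, and a log of patients already picked cannot show who was passed over.

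Some stronger readings are tempting and should be resisted:
- That recruiters are known to be unblinded to arm. The documents are silent; this is an inference.
- That 'typical' acts as a further selection filter. The fixed criteria follow it immediately.
- That one joint consultation could yield two records, because Appendix N counts "Number of eligible children being seen today". The unit is the health worker/caregiver interaction, and the same form asks the age of a single enrolled child. The count makes such visits visible; it does not permit duplicates.
- That three to five patients per worker create the bias. One patient carries 1/5 = 20% to 1/3 = 33% of a worker's round mean, but that is a matter of noise.

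**Conclusion.** The point holds as a design weakness that should be corrected: choice among eligible patients is discretionary in a comparison across arms and rounds, and a less bias-prone rule is available at small cost. It rests on the stated convenience sampling, recruitment after randomisation, rounds identifiable by timing, and the absence of any described masking to arm.

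The direction and size of any bias are unknown. The shifts of 0.1 to 0.5 SD above are assumptions chosen to show sensitivity, not estimates. A reader might also infer a definite figure from a worked case, such as one patient in four scoring 1 SD higher in one arm only, which gives 0.25 SD; that figure is the assumption restated and is not evidence that such a shift would occur. Nor do the documents show that staff or health workers would steer the choice.

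**What to change.** In section 5.5, replace convenience sampling of caregivers with enrolment in order of arrival. On the assessment day, screen under-fives in the selected worker's queue with Appendix L. Each time the team is free, approach the next eligible caregiver, until five interactions are recorded, with a minimum of three. State that each caregiver contributes one interaction per round.

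Keep every screened child on the Appendix L log with the reason for non-enrolment, including a code for eligible but not reached. Add to section 7 a comparison by arm and round of the screened and enrolled numbers, the reasons for non-enrolment and the Appendix N case-mix variables.

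The ceilings of 125 per round and 375 in total are unchanged, and the screening form exists. The cost is some extra screening and waiting, because consent is read and discussed before each consultation; approaching the next eligible caregiver when the team is free, rather than insisting on every consecutive one, limits this. The change does not mask the recruiters, control who joins a given worker's queue, or alter the convenience choice of health workers.

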## **5.6. IN-DEPTH INTERVIEWS**

We plan to conduct IDIs with HFI implementers, health workers from the HFI arm and key stakeholders. The purpose of the IDIs is to collect information on the contextual factors and perceptions of the HFI as it is being implemented as well as the expected and unexpected impacts of the HFI. Written informed consent to conduct the IDI will be obtained from all participants before beginning (Appendix P) as outlined in section 8.2. The IDIs with health workers and implementers will be conducted approximately 9-12 months after the HFI roll-out. The IDIs with key stakeholders will be conducted approximately one year after the HFI roll-out.

Implementer participants for the IDIs will be purposively selected from the ACT PRIME implementation team. Any implementers who delivered health worker training, worked on drug distribution to health centers, or had significant interaction with health workers or district or local officials during the HFI implementation or follow-up period will be invited to participate. We plan to complete up to five IDIs with implementers, following the pre-defined topic guide (Appendix Q).

Health workers from the HFI arm will be selected by convenience sampling. We plan to complete up to 10 IDIs with health workers stationed at HFI health centers, following the pre-defined topic guide (Appendix R).

Key stakeholders will be purposively selected based on their involvement with the ACT PRIME study during the HFI implementation period or their role in the health system. For example, we plan to interview stakeholders involved with drug distribution and staffing for the HFI, district officials including the District Health Officer and Deputy District Health Officer, as well as key staff from the Tororo sub-district and sub-county level. We expect to complete up to ten IDIs with key stakeholders, following the pre-defined topic guide (Appendix S).

## **5.7. SEMI-STRUCTURED QUESTIONNAIRES**

We plan to administer semi-structured questionnaires with health workers from HFI and standard care arms, and private drug shop workers. The purpose of the questionnaires is to collect information on the contextual factors and perceptions of the HFI as it is being implemented as well as the expected and unexpected impacts of the HFI. Written informed consent to conduct the interviews and administer the questionnaires will be obtained from all participants before beginning (Appendix T) as outlined in section 8.2. The interviews with health workers and private drug shop workers will be conducted approximately 9-12 months after the HFI roll-out.

Health workers from HFI and standard care arms will be selected by convenience sampling to ensure at least one health worker from each health facility participates in an interview. We plan to complete up to 10 interviews with health workers in both ACT PRIME arms, 20 in total. The draft questionnaire (Appendix U) will be piloted prior to the onset of the study, and will be refined if necessary.

Private drug shops workers will be randomly selected from the database developed for the Tororo District Survey Project. We plan to complete up to 10 interviews with private drug shop workers. The draft questionnaire (Appendix V) will be piloted prior to the onset of the study, and will be refined if necessary.

## 5.8. FOCUS GROUP DISCUSSIONS

We plan to conduct FGDs with primary caregivers and community health workers from both the HFI and standard care arms. The purpose of the FGDs is to collect information on the contextual factors and perceptions of the intervention as it is being implemented as well as the expected and unexpected impacts of the HFI on communities in the study area. Written informed consent to conduct the FGDs will be obtained from all participants before beginning (Appendix W), as outlined in section 8.2. Participants for FGDs will be selected from the HFI arm and the standard care arm; the same groups of participants will be invited to attend from each arm. The definition of each target population is provided in Table 5.2.

**Table 5.2 FGD target populations**

| Target group            | Definitions                                                                      | FGD characteristics                                                                                                                                                                       |
|-------------------------|----------------------------------------------------------------------------------|-------------------------------------------------------------------------------------------------------------------------------------------------------------------------------------------|
| Primary caregivers      | Person primarily responsible for daily care of young children (generally female) | Groups to be stratified by age (< 30 years vs. > 30 years), health center (communities from each health center in ACT PRIME will be represented)                                          |
| Community health worker | Person providing health care through the Village Health Team                     | Health center (communities from each health center in ACT PRIME study will be represented), distance to a health center (within or outside of a 2km radius of an ACT PRIME health center) |

